### Data collection and measures

#### G-SHPPS and GSHS

The G-SHPPS questionnaire (2021 version) will assess school policies and practices^14^ across seven broad topics (table 1 and online supplemental appendix). Exemplary process indicators are presented under the topics in table 1. School principals of the participating schools will be asked to electronically complete the questionnaire.

**Table 1 T1:** Questionnaire modules of the Global School Health Policies and Practices Survey (G-SHPPS) and sample process indicators

G-SHPPS module	Sample process indicators (Percentage of schools that…)
School Health Services	Routinely provide as part of the health services offered to students counselling to prevent violence (including intimate partner, violence, sexual violence, gender-based violence, bullying, and gang violence). Routinely provide as part of the health services offered to students administration of recommended immunizations. Routinely provide as part of the health services offered to students support for management of overweight and obesity.
School Physical environment	Provide soap and water at handwashing facilities for students. Have improved sanitation facilities for students.
Food and Nutrition Services	Make sugar-sweetened carbonated soft drinks and other sugar-sweetened drinks available to students through the vending machines, stores, canteens, or snack bars on school premises. Routinely make fruits and vegetables available to students through the school’s food and nutrition services. Price healthy foods and beverages in the vending machine, school store, canteen, or snack bar on school premises lower than unhealthy options.
Health Education	Teach health education. Teach sexual and reproductive health and HIV transmission, prevention, and treatment to students. Teach violence and bullying prevention to students. Teach decision-making, problem-solving, goal-setting, and refusal skills to students to help them avoid or reduce health risks.
Physical education	Teach physical education. Teach students as part of physical education the value of physical activity for health, enjoyment, challenge, self-expression, and/or social interaction. Regularly provide recess or other physical activity breaks to students during the school day.
School Governance and Leadership	Have an official council, committee, or team responsible for implementing health promoting school policies, programmes, and activities. Regularly involve and engage parents/caregivers/families and students in developing health promoting school policies.
School Policies and Resources	Have a policy specifically about becoming or continuing to be a Health Promoting School. Have a policy prohibiting use of at least some tobacco or nicotine products, alcohol, and Illicit drugs among students on school premises. Regularly monitor, evaluate, or assess the quality of their health promoting policies, programmes, or activities.

Students’ health behaviours and protective factors will be assessed using the GSHS questionnaire (2021 version)^15^ (see online supplemental appendix). The GSHS is a paper-based, self-administered questionnaire with generic answer sheets that students complete during one classroom period.

The GSHS includes 10 core questionnaire modules. Table 2 presents these modules with exemplary primary outcome indicators. Each city will be encouraged to include all modules. However, up to four modules may be excluded if questions of a specific module are deemed too sensitive. Cities may add context-specific questions, not exceeding a total of 80 questions.

**Table 2 T2:** Questionnaire modules of the Global School-based Student Health Survey (GSHS) and sample primary outcome indicators

GSHS module	Sample outcome indicators, dependent on the city’s choice of modules (percentage of students who…)
Alcohol use	Currently drank alcohol (at least one drink of alcohol on at least 1 day during the 30 days before the survey). Ever drank so much alcohol that they were really drunk one or more times during their life. Had their first drink alcohol other than a few sips before age 14 years, among students who ever had a drink of alcohol other than a few sips.
Dietary behaviours	Were underweight (<−2 SD from median for BMI by age and sex) (measured). Were overweight (>+1 SD from median for BMI by age and sex) (measured). Were obese (>+2 SD from median for BMI by age and sex) (measured). Usually drank carbonated soft drinks one or more times per day during the 30 days before the survey.
Drug use	Ever used cannabis one or more times during their life. Used drugs before age 14 years for the first time, among students who ever used drugs.
Hygiene	Usually cleaned or brushed their teeth less than one time per day during the 30 days before the survey. Never or rarely washed their hands after using the toilet or latrine during the 30 days before the survey.
Mental health	Seriously considered attempting suicide during the 12 months before the survey. Attempted suicide one or more times during the 12 months before the survey. Did not have any close friends.
Physical activity	Were physically active for a total of at least 60 min per day on all 7 days during the 7 days before the survey. Attended physical education classes on 3 or more days each week during this school year. Spent 3 or more hours per day during a typical or usual day sitting or lying down (doing such things as watching television, playing computer games, talking with friends, using their mobile phone, travelling in a motor vehicle, napping or doing other activities sitting or lying down) when not in school or doing homework or sleeping at night.
Protective factors	Missed classes or school without permission on 1 or more days during the 30 days before the survey. Reported that their parents or guardians most of the time or always understood their problems and worries during the 30 days before the survey. Reported that their parents or guardians most of the time or always really knew what they were doing with their free time during the 30 days before the survey.
Sexual behaviours	Ever had sexual intercourse. Had sexual intercourse before age 14 years for the first time, among students who ever had sexual intercourse. Used a condom during last sexual intercourse, among students who ever had sexual intercourse.
Tobacco use	Currently used any tobacco products (used any tobacco products on at least 1 day during the 30 days before the survey). Currently smoked cigarettes (smoked cigarettes on at least 1 day during the 30 days before the survey). Currently used electronic cigarettes (used e-cigarettes on at least 1 day during the 30 days before the survey).
Violence and unintentional injury	Were in a physical fight one or more times during the 12 months before the survey. Were seriously injured one or more times during the 12 months before the survey. Were bullied during the 12 months before the survey.

BMI, body mass index.

Anthropometric measurements of height and weight are taken prior to survey administration. Students receive their measurement results and are asked to subsequently record them on the questionnaire.

Inclusion of the physical activity module will be mandatory to allow for validity testing of some of these questions. Additionally, a new question will be included for validation against the updated WHO physical activity guidelines^10^ reading ‘During the past 7 days* *, did you do at least an average of 60 minutes per day of physical activity across the 7 days?’.

Participating cities will also be encouraged to include the standard GSHS questions on attending school from home during the pandemic, missing classes or school without permission and on school attendance under the influence of alcohol and of drugs.

Once the questionnaire has been finalised for each city, the same questionnaire will be anonymously self-administered by all participating students.

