## Methods and analysis

### Study design and locations

We will conduct a multisite two-armed cluster randomised controlled trial using a nested cross-sectional design. The clusters are defined as schools and classes within schools. The study locations are spread across four world regions and include the cities of Fez, Morocco; Jaipur, India; Saint Catherine Parish, Jamaica; and Sekondi-Takoradi, Ghana. These locations (secondary cities) were purposefully selected in collaboration with WHO regional focal points to generate information for settings that are less likely to be in the focus or receive resources for adolescent health interventions.

In each city, approximately 30 schools will be selected and randomly assigned to either the intervention or control group. At baseline, all sampled schools will conduct a G-SHPPS to assess school policies and practices^14^ and a GSHS to assess risk behaviours and protective factors among students.^15^ Additionally, in the control group of each city, we will conduct studies to validate GSHS physical activity questions against an accelerometer (Axivity AX3^25^) to be worn by students on the wrist for 8 days prior to the baseline survey.

Following the baseline surveys, the intervention schools will participate in data-to-action workshops to develop a package of interventions. Students, parents, teachers, local authorities and researchers will work together to find and prioritise policy and programme solutions to establish a unified action plan. Subsequently, these interventions will be implemented, and study processes and outcomes will be assessed for differential change via repeat G-SHPPS and GSHS surveys after a 2-year follow-up. At follow-up, new classes will be selected from the same schools to ensure participation of 13–17 years old students similar in age to the baseline sample. We hypothesise that the prevalence of behavioural risk factors would be lower and the prevalence of protective factors higher among students in schools in the intervention group compared with the control group at follow-up. An overview of our study design is shown in figure 1.

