### Monitoring and evaluation

As per the Global AA-HA!,^16^ each city’s implementation plan will include process and outcome monitoring through data collected with the G-SHPPS and the GSHS. Progress in the implementation of interventions will be monitored by the team of local stakeholders and WHO on a periodic basis. For each agreed on activity/intervention in the implementation plan, monthly reporting will include whether the activity is not started, in planning, in progress or implemented, with a section for next steps and who is responsible.

Schools in the control arm will operate under ‘business as usual’ within their specific context, that is, they will not receive any intervention selected during the data-to-action workshop.

Follow-up G-SHPPS and GSHS surveys (the same as at baseline) will occur 2 years after the baseline surveys in all selected schools. For the GSHS, new classes from these schools will be randomly selected to ensure participation of 13–17 years old students similar in age to the baseline sample.

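### Four sample primary indicators count only students who already engaged in the behaviour; for the three before-14 indicators at ages 16–17, preventing later onset pushes the odds ratio above 1

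*Protocol article*

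**What the plan says.** The section on the two surveys states: "Table 2 presents these modules with exemplary primary outcome indicators". The table's own labels call the indicators samples that depend on each city's choice of modules. Four of them carry a restricted denominator:

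- Alcohol: "Had their first drink alcohol other than a few sips before age 14 years, among students who ever had a drink of alcohol" (the entry goes on to exclude a few sips).
- Drugs: "Used drugs before age 14 years for the first time, among students who ever used drugs".
- Sexual behaviours: "Had sexual intercourse before age 14 years for the first time, among students who ever had sexual intercourse".
- Sexual behaviours: "Used a condom during last sexual intercourse, among students who ever had sexual intercourse".

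On timing, Study design and locations says: "Following the baseline surveys, the intervention schools will participate in data-to-action workshops to develop a package of interventions". Monitoring and evaluation says: "Follow-up G-SHPPS and GSHS surveys (the same as at baseline) will occur 2 years after the baseline surveys in all selected schools". The follow-up sample is drawn from new classes in the same schools and again covers ages 13–17.

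The hypothesis in Study design and locations, and the one behind the sample size in Study population and sampling, is a lower prevalence of risk factors among students in intervention schools than in control schools. Data management and analysis plan says that most intervention effects will be adjusted ORs from random effects logistic regression, and that a score across several behaviours will also be tested.

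**The concern.** Having ever drunk alcohol, used drugs or had intercourse is a behaviour that the intervention may reduce; ever having had intercourse is itself a Table 2 indicator. If the intervention works, the students who enter these denominators at follow-up differ between arms because of it. Randomisation of schools balances all students; it does not balance the subset who ever engaged. The comparison also answers a different question from the hypothesis, which concerns all students.

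The three before-14 indicators have a second problem. Among older students the numerator event is over before the intervention exists, so the indicator can move only through its denominator. Fewer late starters leave a larger share of early starters. A real benefit would then be reported as a higher proportion with early initiation, which reads as harm on an indicator that the article labels primary.

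**Working it through.** **Inputs from the article.** Follow-up 2 years after baseline; intervention developed after baseline; ages 13–17 at follow-up; reporting groups 13–15 and 16–17; detectable OR 0.75. The article gives no prevalence or onset rate for these behaviours, so all such values below are assumptions.

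**The plan's own figure.** 473 × 1.5 / 0.9 = 788.3, and 4 × 788.3 = 3153.3. This reproduces 788 and 3153. Two of the four cells, half the planned sample, are the 16–17 group.

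**Count.** Indicators per module, in table order: 3 + 4 + 2 + 2 + 3 + 3 + 3 + 3 + 3 + 3 = 29. Four are conditional, and three of those are before-14 indicators.

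**Ages.** Subtract 2 years from age at follow-up:

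| Age at follow-up | Age at baseline | Time from baseline to 14th birthday |
|---|---|---|
| 13 | 11 to under 12 | 14 not yet reached at follow-up |
| 14 | 12 to under 13 | over 1, up to 2 years |
| 15 | 13 to under 14 | at most 1 year |
| 16 | 14 to under 15 | already passed |
| 17 | 15 to under 16 | already passed |

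An ever-user aged 13 must have started before 14, so the three indicators are 100% at that age by definition.

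**Algebra.** As shares of all students, let E be onset before 14 and L onset at 14 or later (0 = control, 1 = intervention). The indicator is E/(E + L), with odds E/L. Hence

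OR = (E1/E0) × (L0/L1).

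**Ages 16–17.** E predates the intervention, so randomisation makes E1 = E0 in expectation and OR = L0/L1. This exceeds 1 whenever later onset is reduced.

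- Simple illustration: E = 12%, L0 = 18%, and a quarter of later starts prevented, so L1 = 13.5%. Ever-use falls from 30% to 25.5%. The indicator rises from 12/30 = 40% to 12/25.5 = 47%. OR = 18/13.5 = 1.33.
- With the planned OR of 0.75 applied to later onset, L1 = 0.75·L0/(1 − 0.25·L0), so OR = (1 − 0.25·L0)/0.75. For L0 = 5% this is 0.9875/0.75 = 1.32; for L0 = 30% it is 0.925/0.75 = 1.23. E does not enter.
- Example with E = 10%, L0 = 20%: L1 = 15.8%. Ever-use falls from 30.0% to 25.8% (OR 0.81, the right direction), while the indicator rises from 33.3% to 38.8% (OR 1.27).

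**Ages 13–15.** Early onset can also fall, so both factors matter. The OR is above 1 if later onset falls proportionally more than early onset, and below 1 in the opposite case. A constant onset hazard of 3% or 6% a year from age 10, cut by 25% after baseline, gives about 1.20 to 1.21 at ages 13–15, 1.18 to 1.19 at 16–17, and 1.16 with all ages pooled. The first and last of these depend on the assumed hazards for their sign as well as their size.

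**Condom use.** There is no age cut-off, and the behaviour is one that the intervention could change. The denominator is still selected after randomisation. The direction of bias depends on whether the students who refrain from intercourse because of the intervention would have used condoms more or less often than the rest, which the article does not tell us.

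**The case against.** The strongest reply is that these are sample indicators in modules that a city may drop. Up to four modules can be excluded as too sensitive, and only three are affected. Each city also chooses its targets after baseline; where alcohol, drugs or sexual behaviour is not addressed, the denominators may hardly move. The same modules contain all-student indicators (current drinking, ever drunk, ever used cannabis, ever had intercourse), where a real benefit would show. The article does not list which indicators will be compared between arms, and the full analysis plan is not shown. All of this stands. It limits the reach and lowers the severity, but does not remove the point: the article writes the conditional denominators out, calls the indicators primary, and plans between-arm ORs.

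Three stronger readings are tempting and not supported:

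- That the three before-14 indicators are fixed at ages 16–17. Only the numerator event is fixed. The indicator moves through its denominator, and that movement produces the reversal.
- That all four indicators reverse. The result covers the three before-14 indicators only; condom use has the selection problem without a known direction.
- That reversal is certain at every age. It follows from the timing at 16–17; at 13–15 it rests on assumed onset rates.

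Two features of the planned analysis might seem to help. Random effects deal with clustering, not with who is in the denominator. Comparing change from baseline does not help either, because the follow-up denominators still differ through the intervention's own effect.

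**Conclusion.** The point holds in this form and is a should-fix. Four of 29 sample primary indicators condition on a post-randomisation behaviour and do not match the all-student hypothesis. For three of them, in the 16–17 group, an intervention that prevents onset at 14 or later gives an expected OR above 1: about 1.23 to 1.32 if later onset has a true OR of 0.75 and a control share of 5–30%. The sign in that group does not depend on the assumed prevalences; the size does. It does require that early onset is balanced by randomisation, with no difference between arms in student movement or in how age at onset is reported. The ORs are crude, so a school-adjusted estimate may differ in size.

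A reader might infer that the trial's overall conclusion would be inverted. The article does not support that, given the all-student indicators alongside and the cities' freedom to omit these modules.

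**What to change.** 1. Keep the four conditional indicators for the descriptive fact sheets.
2. For arm comparisons, and for the composite score if these items enter it, use all students as the denominator. Ever-use or current use should be the main choice. These are in Table 2 already or follow from the same items, since the conditional denominators require ever-use to be known.
3. If a before-14 measure is kept for arm comparisons, compute it among all students aged 14–15 at follow-up. State its limited sensitivity: 15-year-olds had at most one year between baseline and age 14, less the time taken by workshops and planning. At 16–17 an all-student version has an expected OR of 1.00: no reversal, but no information on effect.
4. Report condom use among students who ever had intercourse as descriptive. Alternatively, add intercourse without a condom at last intercourse among all students, and state that it combines abstinence with condom use and is a different construct.

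The cost is recoding and a short statement in the analysis plan before the follow-up analysis; no new data are needed. The downside is that the effect-analysis indicators will no longer match the standard fact-sheet definitions, so the two sets need clear labels.

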#### Additional measures

With the interventions of the present study aiming at improving students’ health and including programme planning, policy and structural change, it is hypothesised that a range of secondary outcomes would also be positively influenced. These secondary outcomes will depend on the topics and interventions selected by each city during the data-to-action workshop and will be identified on finalisation of each city’s action plan. They may include school absenteeism and performance among learners in the intervention schools, improved healthcare seeking, secondary health outcomes and improved communication of adolescents with teachers and parents.

#### Physical activity validation study

In addition to the GSHS self-reported physical activity, activity data will be collected using the Axivity AX3 accelerometer. This device has previously been used in large-scale population-based^27 28^ and school-based studies.^29^ The Axivity AX3 records movement, and reports raw acceleration signals in real time, allowing for transparent analysis.^30^

From each school in the control group, one class will be randomly selected to participate in testing the validity of questions currently used in the GSHS to assess student’s physical activity, sedentary behaviour and sleep, and the new question that was added to assess WHO’s 2020 physical activity guidelines.^10^ Every student in the selected classes will be asked to participate (approximately 300 students per city).

Participation in the physical activity validation study is voluntary. Participating students will be asked to provide written assent, and their parents or guardians will be asked to provide written consent (see online supplemental appendix).

In the week prior to the GSHS baseline survey, selected students will wear the Axivity AX3 on their non-dominant wrist continuously for 8 consecutive days.^31^ Trained personnel will instruct students to wear the waterproof device and to participate in all their normal activities. After having worn the accelerometer, students will be asked to participate in the GSHS survey at baseline. Axivity AX3 data will then be compared with data collected with the GSHS physical activity module and the added physical activity question.

### Interventions

This study’s intervention approach is embedded in the framework of the Global Standards for health promoting schools and its concept of a whole-school approach to promoting health.^18^ Schools in the intervention arm will implement health promotion strategies to address the most critical health risk behaviours and protective factors, considering the eight Global Standards including government policies and resources; school policies and resources; school governance and leadership; school and community partnerships; school curriculum; school social-emotional environment; school physical environment; and school health services.

Following the baseline surveys, students in the intervention arm will receive instructions to participate in photovoice.^22^ This is an established^23 24^ qualitative participatory method through which adolescents can pictorially take impressions of health facilitators and barriers in their school and community. Pictures will be uploaded onto a secure platform, reviewed and sorted by trained personnel, ensuring that no inappropriate photos are included.

To develop the interventions, data-to-action workshops will be held in each city (see online supplemental appendix for agenda). They will be facilitated by the local study coordinator and WHO and UNESCO personnel and include a minimum of three nominated students from each intervention school, teachers, parents and up to five local authorities and researchers. The nomination of students for the workshops will be based on the student’s interest in participating and ensure gender balance.

Data-to-action workshops will use the data collected during the baseline surveys, the photovoice pictures and follow the Global AA-HA! approach and its three key steps^16^: First, recognising that the health needs are different in each city, a needs assessment will be done, using the GSHS data and the photovoice pictures. To facilitate this, for the workshop, data will be visualised in an easy-to-understand summary format, including fact sheets and infographics. Workshop participants will review the site-specific results to identify which conditions, health risks and determinants need to be addressed most urgently. Second, considering that the situation adolescents live in is different in each setting, in a landscape analysis, results from the local G-SHPPS will be reviewed, along with other existing programmes, policies and legislation. Similar to step one, results will be summarised in an easy-to-understand format and used to identify gaps and potential areas for improvement. Step two will also include a review of evidence-based interventions of the Global AA-HA! and a meta-analysis,^11^ prepared in a format that will speak to workshop participants. Third, specific actions will be identified to address the issues specific to each city, considering the outcomes of steps one and two. Identified actions will be prioritised, considering availability of resources, effectiveness, feasibility, capacity to implement, cultural appropriateness and focus on structural and systems-oriented changes.

This participatory approach will ensure that—while considering the adolescents’ health needs and each city’s situation—the selected interventions will be based on evidence, be feasible, appropriate, acceptable and aligned with local priorities. For example, a set of interventions to decrease tobacco use might be selected for a city with a high prevalence of tobacco use among students. These might include individual-level and interpersonal-level interventions, but also school policy changes such as the introduction of smoke-free school policies that would ultimately lead to sustained behaviour change.

The workshop duration will be 3 days, and include students, parents and teachers for at least 2 hours per day. To ensure that adolescents are meaningfully engaged, existing guidelines on adolescent participation and civic engagement will be followed.^32^ Breakout sessions will be organised during the workshops for which the different stakeholders will be separated, to ensure that each stakeholder group gets their own space to express their views. The different views will be brought back to the plenary and integrated as appropriate. Students will also get the opportunity to comment on and add to actions proposed by other stakeholders.

Each city will develop a 2-year implementation plan based on the prioritised interventions. These will be classified by topic and implementation level, including structural, environmental, organisational, community, interpersonal and individual level. A team of local stakeholders will be identified with clear responsibilities regarding implementation of the interventions, and additional technical support will be provided by WHO.

